### Definition of a serious adverse event

Any event that results in death, a life-threatening adverse event, inpatient hospitalisation or prolongation of existing hospitalisation, a persistent or significant incapacity or substantial disruption of the ability to conduct normal life functions, or a congenital anomaly/birth defect is deemed a serious adverse event.

### Event reporting

All adverse events will be reported directly to either the site or principal investigator. Recurrent adverse events or serious adverse events in isolation will be reported in turn to the local ethical committee and the risk assessment department for risk analysis. Indications for premature trial cessation are discussed in the ‘Protocol violations’ section.

### Trial audit

Regular audit of trial conduct shall be undertaken throughout the study period. The project management group ([name]) shall convene monthly to review trial proceedings internally and address any methodological, clinical and ethical concerns. External review shall be undertaken every 6 months by the local research ethics committee with further data monitoring from an independent research advisor from the National University of Ireland, Galway.

## Statistical considerations

Once randomisation and intervention is complete, patient outcomes will be assessed using an intention-to-treat analysis. All losses to follow-up at any time-point will be recorded and reported. A research statistician will conduct all analyses independently. Statistical analysis will be conducted using SPSS Version 21 (IBM Corp, Aramonk, NY) The primary feasibility outcome will be reported as the percentage of all eligible patients who agree to participate in the feasibility study. Descriptive data will be provided at baseline and at each follow-up to define variations among and within groups. Continuous data will be presented as mean and standard deviations with confidence intervals of 95%. Categorical data will be reported as frequencies with chi-square or Fischer’s exact *t* test used for comparative data. Where data is not normally distributed, non-parametric tests will be utilised as applicable. Further subgroup and regression analyses will be undertaken to adjust for confounding variables known to affect ulcer healing including age, duration, mobility and size. A *p* value of < 0.05 will be deemed significant.

Contemporary data suggests a median healing time of about 20 weeks for patients with a venous ulcer treated by superficial venous ablation [23]. Assuming a median time to healing in the control arm (those treated with superficial venous ablation and compression alone) of 140 days would be reduced to 110 days by the addition of iliac vein intervention where necessary (i.e. a 20% relative reduction in healing time) would require 270 patients in each arm of the trial, i.e. 540 in total. Allowing for a 10% withdrawal and dropout rate increases the required sample size to 594 patients. In advance of undertaking such a large trial, we aim to undertake a feasibility phase in order to assess eligibility, recruitment rates and provide baseline data for a refined sample size calculation. For this feasibility phase, we aim to recruit 30 patients to each trial arm.

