#### Primary efficacy outcomes

The primary efficacy outcome will be the proportion of ulcers healed 3 months following the overall intervention and the iliac vein patency in the interventional group.
A healed ulcer is defined as complete re-epithelialization with no scab and no requirement for dressing [17].

Stent patency will be evaluated by ultrasound within 24 h, at 6 months, 1 year and annually thereafter. One-year patency rates will be reported alongside the primary efficacy endpoint. Five-year patency rates will be reported in a separate long-term follow-up report. The following will be reported with respect to patency:
Primary patency: patent stent with less than 20% in-stent or between stent stenosis and no re-interventionsPrimary assisted patency: patent stent with less than 20% in-stent or between stent restenosis which has undergone re-intervention to prevent occlusionSecondary patency: patent stent which has been reopened following occlusionStent occlusion: stent with a no-flow segment which has not undergone re-intervention or in which re-intervention failed

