##### Re-intervention

Freedom from re-intervention will be presented for 1 -year and 5-year follow-up reports. Both superficial and deep venous re-interventions will be recorded.

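### The stated rule for continuous data gives time to ulcer healing no value for unhealed patients, so feasibility estimates taken under it would mislead the refined sample size

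*Protocol article*

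**What the plan says.** The Secondary outcomes section of the protocol article lists time to ulcer healing, measured in days. The Statistical considerations section has no rule specific to it. Its general rules are:

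- Continuous data: "Continuous data will be presented as mean and standard deviations with confidence intervals of 95" per cent.
- Non-normal data: "Where data is not normally distributed, non-parametric tests will be utilised as applicable".
- Categorical data: chi-square or an exact test.
- Adjustment: "Further subgroup and regression analyses will be undertaken to adjust for confounding variables known to affect ulcer healing", with age, duration, mobility and size named. The type of model is not given.
- Analysis is by intention to treat, and losses to follow-up are reported.

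The same section sizes the main trial on healing time. It starts from "Assuming a median time to healing in the control arm", put at 140 days from a cited source, and reduces it to 110 days. It arrives at 270 patients per arm, 540 in total, or 594 after a 10% allowance for dropout. One purpose of the feasibility phase is to "provide baseline data for a refined sample size calculation". The Interim analysis section adds a look once 30 patients have 6 months of follow-up, to help power the trial. The Crossovers section offers iliac investigation and treatment to unhealed controls at 6 months, and to controls with a history of iliofemoral DVT at 3 months.

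**The concern.** Healing time is known only for patients who have healed. For the rest, all that is known is that it exceeds their follow-up. A mean and SD cannot use that information, so applying the continuous-data rule to this outcome leaves an analysis of healed patients. Selecting on healing shortens the times in both arms and pulls the arms together, because slow healers are removed from each and more are removed from the slower arm.

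The sizing paragraph reasons in medians, and its total fits a method that handles unhealed patients by censoring. The analysis wording and the planning therefore do not match. What is at stake is the refined sample size. If the control median or the treatment effect is read from healed patients, the main trial is planned on the wrong number, and the error is largest at short follow-up, which is when the interim look takes place.

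**Working it through.** **1. Reproduce the plan's figure.** Inputs from Statistical considerations: medians 140 and 110 days, and "value of < 0.05 will be deemed significant". Allocation is 1:1 (Statement of design). Sidedness and power are not stated; two-sided 5% and 80% are assumed. Under exponential healing the ratio is 110/140 = 0.786. Schoenfeld's formula:

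events = 4 × (1.960 + 0.842)² / (ln 0.786)² = 4 × 7.849 / 0.05816 = 539.8, so 540.

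This is the stated total exactly, and 540 × 1.10 = 594. Nearby alternatives do not give 540: Freedman's formula gives 546, 90% power gives 723 and a one-sided test gives 426. The match supports a log-rank basis, although the article does not name one.

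**2. What a healed-only summary would show.** Let m be the true median and τ the follow-up in days. With no dropout or crossover:

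- Proportion healed: F = 1 − 2^(−τ/m)
- Median among the healed: −m × log₂(1 − F/2)
- Mean among the healed: m/ln 2 − τ(1 − F)/F

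Worked for control at 6 months (τ = 182): F = 1 − 2^(−1.3) = 0.594. Median = −140 × log₂(0.703) = 71.2. Mean = 202.0 − 182 × 0.406/0.594 = 77.5 (from unrounded values).

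| Follow-up | Healed, control v intervention | Healed-only medians | Ratio | Healed-only means |
|---|---|---|---|---|
| 6 months (182 d) | 59% v 68% | 71.2 v 66.2 | 0.93 | 77.5 v 74.0 |
| 12 months (365 d) | 84% v 90% | 109.3 v 94.8 | 0.87 | 130.3 v 118.0 |
| 2 years (730 d) | 97% v 99% | 134.6 v 108.4 | 0.81 | 181.8 v 151.3 |
| True values | – | 140 v 110 | 0.786 | 202.0 v 158.7 |

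The true 30-day gap in medians becomes about 5 days at 6 months and 14.5 at 12 months. The true 43-day gap in means becomes 3.5 and 12.3 days.

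**3. The interim look.** Of 30 patients, about 15 are controls. At 6 months 1 − 0.594 = 41% of them, about 6, would have no healing time.

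**4. Effect on a refined size.** The same formula is used, with unrounded healed-only medians:

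- Effect taken as the healed-only ratio: about 6,082 events (6 months) or 1,558 (12 months).
- Effect kept at 30 days on the shortened control median: 41.2/71.2 gives about 105 events (6 months); 79.3/109.3 gives about 305 (12 months).
- Effect kept as the same relative reduction: 540, unchanged.

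The direction of the error depends on which quantity is carried forward.

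**5. Sensitivity to the assumed median.** The Discussion cites a trial with a 56-day median under early ablation. With m = 56 and τ = 168 (24 weeks), F = 0.875 and the healed-only median is −56 × log₂(0.5625), about 46 days. The bias is smaller when healing is faster.

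**The case against.** The strongest reply is that the quoted sentence is a general presentation rule that does not mention healing time, and that nothing in the article orders a healed-only analysis. The log-rank test is non-parametric and Cox is a regression, so the wording on non-parametric tests and on regression excludes neither. Intention to treat argues against dropping unhealed patients. Healing time is secondary, and a condensed article may leave method detail to another document. In this trial "The primary efficacy outcome will be the proportion of ulcers healed 3 months following the overall intervention", together with iliac vein patency, and the stated categorical tests suit that proportion.

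Much of this stands, and it rules out several stronger readings that a reader might infer:

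- **That healing time is covered only by methods confined to healed patients.** Rank tests can place unhealed patients last. In simulation with 270 per arm, such a test has power 0.58 at 6 months and 0.67 at 12, against 0.62 and 0.75 for log-rank. A healed-only rank test has 0.10 and 0.28, but the article does not prescribe one.
- **That power is lost in this phase.** With 60 patients, about 38 healing events at 6 months and 52 at 12 months give even the log-rank test only about 11% and 14% power.
- **That re-intervention has the same defect.** The article says "Freedom from re-intervention will be presented for 1 -year and 5-year follow-up reports". It does not say that a plain proportion will be used.
- **That the current 540 rests on a biased median.** The 140 days is external.

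The bias also fades with follow-up and is gone by 5 years. That helps little with resizing: the interim look is at 6 months, and the Status of trial section runs from July 2019 to September 2020, about 14 months.

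The objection does not remove the mismatch. The one explicit rule for continuous data cannot be applied to unhealed patients, the sizing fits a time-to-event method, and the article says that feasibility data will feed the next calculation.

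**Conclusion.** The point holds as a mismatch between the stated analysis rule and the stated planning, and it should be corrected before any resizing. If the mean/SD rule is applied to healing time, the control median would come out near 71 days at 6 months or 109 at 12 months instead of 140, and the ratio near 0.93 or 0.87 instead of 0.786. A refined main-trial size could then be several times too large or too small, or unchanged if only the relative reduction is carried forward.

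These figures assume exponential healing at the plan's medians, two-sided 5%, 80% power, and no dropout or crossover. The article does not say that healing time is the quantity to be refined. That is the natural reading, because the existing calculation rests on it. Neither the primary efficacy outcome nor the present sample size is affected by this point.

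**What to change.** Add to Statistical considerations:

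- Time to healing is measured from randomisation. This keeps ulcers that heal before the procedure in the analysis, as the Ulcer assessment section intends.
- It is summarised by Kaplan-Meier (median with 95% CI) and compared by the log-rank test and by Cox regression adjusted for the covariates already listed: age, ulcer duration, mobility and size. Patients unhealed at last assessment are censored there.
- The Kaplan-Meier control estimate is used for resizing, including at the interim look.
- The comparison is by intention to treat, and the main between-arm comparison is limited to 6 months, when unhealed controls are offered iliac treatment.
- Six months is not free of crossover, because controls with a history of iliofemoral DVT receive the offer at 3 months. Report these patients separately and add a sensitivity analysis, for example one that leaves out patients with that history in both arms.

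The cost is a few lines of text. Healing reports, visit dates and the covariates are already to be collected, and the named software fits these methods. The baseline list already includes previous deep venous thrombotic events; the site must be identifiable for the sensitivity analysis.

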### Interim analysis

Once 30 patients have been recruited and followed up for 6 months an interim analysis shall be undertaken to guide recruitment and further inform trial design with a view to powering the trial appropriately.

## Ethical considerations

### Ethical approval

Ethical approval has been approved centrally by the Galway Clinical Research Ethics Committee, Galway, Ireland. The ethics committee reference is C.A. 2111. Of note, recruitment shall not commence at any other centre until full ethical approval has been confirmed with the local ethical committee.

### Data protection

All data shall be managed in the strictest confidence by approved trial investigators in accordance with Irish data-protection law. Datasets will be anonymous, encrypted and stored onsite only.

## Discussion

The management of lower limb venous ulceration continues to raise significant debate particularly, in more recent years, with regard to adjunctive surgical intervention. At present, conservative measures including regular ulcer dressing with compression bandaging are well established. This approach offers undoubted benefits improving both ulcer healing rates and reducing recurrence [5, 24] in the longer term. However, this approach can be slow with a median ulcer healing time of up to 99 days [5] and high rates of non-compliance [24]. As such, more efficient treatment protocols continue to be investigated.

The recent publication of the EVRA trial [17] has further enhanced the concept that early surgical intervention can improve treatment protocols in the venous ulcer cohort. Included patients randomised to the intervention group of early endovenous intervention in conjunction with compression therapy experienced a significantly shorter time to ulcer healing. The authors identified a median ulcer healing time of 56 days in the treatment group compared to 82 in the control group among 450 patients. Furthermore, they identified an impressive overall healing rate of 85.6% at 24 weeks compared to 76.3%. This data consolidates evidence from the ESCHAR study [25] which confirmed lower ulcer recurrence rates at 12 months following combined intervention with surgery and compression therapy. As a result of these data a combined approach to venous ulceration is now widely advocated [26].

Thus, while it would appear that dual intervention offers benefit to ulcer patients a significant proportion of those affected may have concomitant NIVL’s [16] contributing to the venous hypertensive pathophysiology. This further exposes patients to delayed, non-healing and recurrent ulceration. At present, these lesions go largely unnoticed due to inadequate peri-operative imaging with access to MRV and CTV often resulting in further treatment delays and the added risks of contrast exposure. Intravascular ultrasound offers proven [27], minimally invasive imaging of the ilio-femoral segment simultaneously with superficial venous ablation. This provides the treating physician with a real-time assessment of NIVL’s and the ability to concomitantly treat significant lesions thus reducing risk of persistent venous hypertension.

This randomised controlled feasibility trial aims to provisionally assess the merits and safety of adjunctive procedural IVUS, stenting, endovenous ablation and compression therapy in the treatment of venous ulceration. To date, there is a paucity of data addressing this important health issue, and consequently, there is a need for well-designed large randomised studies examining the hypothesis.

Due to the significant number of patients required to adequately power this trial an initial feasibility trial on 60 patients will be carried out. This period will be used to assess trial flow, recruitment and the initial efficacy of treatment. Should the initial trial be successful the authors plan a multi-centre approach to allow for adequate and timely patient recruitment and treatment with a view to definitively identifying the role of iliac intervention in this cohort.

## Status of trial

Protocol: 1. V8

Recruitment: Commencing July 2019

Estimated Completion: September 2020

## Data Availability

Anonymous data and materials will be encrypted and stored in the secure server within the Lambe Research Institute, National University of Ireland. Data will be available upon suitable request to the senior author.

## Abbreviations

ABPI: Ankle-brachial pressure index
CT: Computed tomography
eGFR: Estimated glomerular filtration rate
LAR: Luminal area reduction
MR: Magnetic resonance
NIVL: Non-thrombotic iliac vein lesion
PTS: Post-thrombotic syndrome
BWAT: Bates-Jensen wound assessment tool
IVUS: Intravascular ultrasound
